## Data Analysis

Missing data will be examined to determine if missing completely at random (Little, 1988) and multiple imputation implemented if required, the gold standard approach to handling missing data (Graham, 2009). Data will be checked for normality of distribution (e.g., skewness, kurtosis). Independent sample *t*-tests will investigate systematic differences in baseline characteristics between groups to identify potential co-variates for inclusion in the main analysis. A series of 2 × 2 (Treatment×Time) mixed between-within ANOVAs will be conducted with intention to treat analysis to (1) compare the CO-OP-I group with WLC to determine preliminary efficacy (Time: pre, post) on goal attainment, skill transfer, perceived executive function and functional performance; (2) compare the CO-OP-I group with WLC to determine changes (pre, post) in self-efficacy and health-related QoL; and (3) compare CO-OP-I and CO-OP-S groups on key outcomes (pre, post, and follow-up) to determine optimal program intensity and explore potential for long-term maintenance and generalization of skills. Interviews will be analyzed using the process of inductive thematic analysis as described in Braun and Clarke (2006) and this qualitative data along with clinician field notes will inform the analysis of feasibility parameters in terms of acceptability, demand, adaptation, and expansion (Bowen et al., 2009).

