### Procedures

The study will be advertised online on the Parkinson's Queensland Research Participation Opportunities page, on their social media platforms and via the member's newsletter. Potential participants will self-select and contact the interventionist if they are interested in participating in this research. During first contact via telephone, the interventionist will undertake eligibility and cognitive screening, provide participants with information about the study, and obtain verbal consent to participate. Potential participants will be emailed a copy of the participant information and consent form to aid their decision-making process with regards to study participation. Study participation will be offered if eligible and score above the cut-off for the telephone Montreal Cognitive Assessment (T-MoCA). Participants will be emailed the link to the online survey once the offer of participation is verbally accepted. The online questionnaire collects demographic and disease information and self-report outcome measures and will be completed independently by participants, outside session times. The interventionist will then complete a home visit to complete baseline assessments and program goal setting facilitated by the Canadian Occupational Performance Measure (COPM) will occur. Hard copies of the participant information and consent forms will be provided to participants during the first home visit, and written consent obtained. Using the prioritized goals identified during the COPM interview, Goal Attainment Scales (GASs) for each goal will be created to enable objective measurement by an independent assessor, according to the procedure used previously for the combined use of the COPM and GAS (Doig et al., 2010). Baseline performance in goal activities will be recorded objectively to enable independent ratings of goal performance by a masked assessor. Following this visit, participants will be randomly assigned to either the CO-OP-I or a WLC with a blocked equal allocation, stratified by scores on the Addenbrooke's Cognitive Evaluation – III (ACE-III), by a computer-generated randomization schedule. A summary of the timeframes for consent, screening, goal setting, randomization, and outcome measurement across the phases of the study are outlined in Table 1.

**Table 1 table1-00084174231156287:** Phases of Study

	Enrolment	Baseline	Intervention		Follow-up

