Timepoint		*T1: prior to intervention*	*T2: 10 weeks*	*T3: (20–22 weeks)*	*T4: (30–32 weeks)*
Enrolment					
Eligibility; T-MoCA	✓				
Informed consent	✓				
Goal setting conducted using COPM and GASs established		✓			
Random allocation		✓			
Assessments:					
Age; sex; education level; work status; disease duration; medication; ACE-III; NART; H&Y		✓			
Primary outcomes: COPM; GAS; PQD		✓ Both groups—baseline measurement	✓ Post-WLC/ pre CO-OP-S ✓ Post-CO-OP-I	✓ Post-CO-OP-S ✓ CO-OP-I 3-month follow-up	✓ CO-OP-S 3-month follow-up
Functional outcomes: HADS; AS; PDQ-8; FSS; GSE; DLSES; NEADL;S&E		✓ Both groups—baseline measurement	✓ Post-WLC/ pre CO-OP-S ✓ Post-CO-OP-I	✓ Post-CO-OP-S ✓ CO-OP-I 3-month follow-up	✓ CO-OP-S 3-month follow-up

Abbreviations: AS = Apathy Scale; ACE-III is Addenbrooke's Cognitive Evaluation – III; COPM = Canadian Occupational Performance Measure; CO-OP-S = CO-OP standard intervention; CO-OP-I = CO-OP intensive intervention, DLSES = Daily Living Self-Efficacy Scale; FSS = Fatigue Severity Scale; GAS = Goal Attainment Scale; GSE = General Self-Efficacy Scale; HADS = Hospital Anxiety and Depression Scale; H&Y = Hoehn and Yahr Scale; NART = National Adult Reading Test; NEADL = Nottingham Extended Activities of Daily Living Scale; PDQ = Perceived Deficits Questionnaire; PDQ-8 is Parkinson's Disease Questionnaire – Short Form; S&E is the Schwab and England Activities of Daily Living Scale; T-MoCA = Telephone Montreal Cognitive Assessment; WLC = waitlist control.

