#### Demographic and Disease Data

Demographic and disease data collected at baseline via an online Qualtrics survey includes age, sex, education level, work status, disease duration, and medical management (i.e., levodopa dosage). Data collected in person during the initial home visit will include pre-morbid IQ, neuropsychological status, and disease severity.

The National Adult Reading Test (NART) (Nelson & Willison, 1991) is a 50-word reading test that provides reliable and valid estimates of IQ and has been shown to be relatively insensitive to the effects of various neurological conditions, including PD (Mathias et al., 2007). The NART will be used in this study to estimate the premorbid intelligence levels of participants to describe the study sample.

The ACE-III (Mioshi et al., 2006) is a brief cognitive screening battery assessing five neuropsychological domains (orientation and attention, memory, verbal fluency, language, and visuospatial function). The ACE-III score will be used to stratify participants for randomization. The stratification groups are no cognitive impairment and MCI. The cut-off score for this assessment will be 88 whereby a score of 100–89 is considered no cognitive impairment and a score of 88–77 is considered MCI (Senda et al., 2020).

The Modified Hoehn and Yahr (H&Y) scale (Hoehn & Yahr, 2011) is a 7-point Likert scale that focuses on the clinical impression of overall PD severity based on key aspects of disability and features of objective impairment. The H&Y scale will be used to measure disease severity/stage.

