#### Tertiary and Feasibility Outcome Measures

The tertiary outcome measures will be administered as self-report questionnaires via the online Qualtrics survey at pre, post-WLC, post-CO-OP, and follow-up assessment time points. These covariates have been included to describe the study participants and explore whether these common symptoms impact the feasibility of the approach.

The Hospital Anxiety and Depression Scale (HADS) (Zigmond & Snaith, 1983) is a 14-item scale that focusses on the emotional aspects of depression and does not include physical and cognitive symptoms. This is appropriate in the context of this study as cognition and motor symptoms are assessed separately. The HADS will be used to measure depressive symptoms and mood.

The Fatigue Severity Scale (FSS) (Herlofson & Larsen, 2002) is a 9-item fatigue rating scale that emphasizes the functional impact of fatigue and contains items on physical and mental fatigue and social aspects. Items are rated on a 7-point Likert scale. The FSS will be used to describe and measure participant's fatigue levels.

The Apathy Scale (AS) (Starkstein et al., 1992) is a 14-item apathy rating scale that is used to screen for and to assess the severity of apathy in PD. Questions are answered on a 4-point Likert scale. The questions are typically read aloud to the participant by the clinician but will be administered in self-report format in this study to allow for inclusion in the online survey. The AS will be used to measure apathy.

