## Random Allocation

Participants will be randomly assigned to either the CO-OP-I or a WLC group using blocked allocation, stratified by scores on the ACE-III. An independent senior member of the research team will create a computer-generated randomization schedule with concealment then allocate participants in chronological order from time of written consent.

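### Choosing covariates by baseline t-tests between randomised groups flags only chance imbalance; the T1 outcome and the ACE-III stratum should be prespecified instead

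*Protocol article*

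**What the plan says.** In the protocol article, Data Analysis, independent-sample t-tests "will investigate systematic differences in baseline characteristics between groups to identify potential co-variates for inclusion in the main analysis". No alpha is given for these tests, and no other basis for choosing covariates is stated. The main models follow: 2 × 2 Treatment × Time "mixed between-within ANOVAs will be conducted with intention to treat analysis", with pre and post as the two levels of Time for the comparison of CO-OP-I with WLC.

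The groups being tested are randomised. Procedures says they are formed "with a blocked equal allocation, stratified by scores on the Addenbrooke's Cognitive Evaluation – III (ACE-III), by a computer-generated randomization schedule". Random Allocation adds that "An independent senior member of the research team will create a computer-generated randomization schedule with concealment". Under Demographic and Disease Data, "The ACE-III score will be used to stratify participants for randomization", with two strata split at a score of 88.

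Table 1 lists these baseline characteristics: "Age; sex; education level; work status; disease duration; medication; ACE-III; NART; H&Y". The tertiary measures (HADS, FSS and AS) are also called covariates: "These covariates have been included to describe the study participants and explore whether these common symptoms impact the feasibility of the approach".

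**The concern.** A t-test between arms asks whether the groups differ on a variable. A covariate earns its place in the model by predicting the outcome. After concealed randomisation the first question has a known answer: any difference is chance, so there is nothing systematic to find. The second question is never asked.

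The rule also pulls against the design. Allocation is made "using blocked allocation, stratified by scores on the ACE-III", which balances ACE-III and so makes it one of the variables least likely to be flagged. Yet the stratification factor is the variable that belongs in the analysis by design.

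At stake are the precision of the efficacy estimates and the independence of the adjusted model from the observed data. Sex and work status, both on the list, are also categorical and do not suit a t-test.

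**Working it through.** **Inputs.** From the article: concealed 1:1 allocation stratified by ACE-III; nine baseline characteristics in Table 1; three further measures called covariates; a 2 × 2 pre-post mixed ANOVA. Not in the article, so assumed: alpha of 0.05 for the baseline tests, 20 per arm (range 10 to 30), a true effect of 0.8 SD, and correlations as shown. The article gives no figure to reproduce.

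**1. How often a covariate is flagged.** Under randomisation the null of equal baselines is true, so P(flag) = alpha for each variable, whatever its prognostic strength. Simulation (10,000 runs per setting, 10 to 30 per arm, covariate-outcome correlation 0.3 to 0.7) gave 4.6% to 5.3%. A prognostic covariate is thus omitted about 95% of the time, and still 90% at alpha 0.10 or 80% at alpha 0.20. Two independent prognostic covariates are both omitted with probability 0.95² = 0.90.

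**2. The stratifier.** With allocation balanced within two equal strata of a covariate, the t-test flagged that covariate in 0.1% to 0.2% of runs. Leaving it out at a correlation of 0.5 made the treatment test conservative: type I error 0.032 to 0.034, against about 0.05 when it was included.

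**3. Chance of at least one flag.** With k independent tests, P = 1 − 0.95^k. For all nine Table 1 items it is 1 − 0.95^9 = 37%; with HADS, FSS and AS added, 1 − 0.95^12 = 46%. Both are rough upper figures. Removing ACE-III and the three items least suited to a t-test (sex, work status, education level) leaves five: 1 − 0.95^5 = 23%. Correlation among items changes these again.

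**4. What the Time factor already does.** With two time points, the Treatment × Time test is the between-group comparison of post minus pre. In units of the outcome SD, with pre-post correlation r, the residual variance is 2(1 − r) for the change score and 1 − r² for ANCOVA on T1. The ratio is (1 − r²)/[2(1 − r)] = (1 + r)/2, that is 0.65, 0.75, 0.85 and 0.90 at r = 0.3, 0.5, 0.7 and 0.8. ANCOVA is more precise at each of these values, and the gain shrinks as r rises.

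**5. Power** (20 per arm, effect 0.8 SD, 10 candidate covariates including the T1 score, two-sided 0.05):

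| r | Change score with t-test screening | ANCOVA on T1 |
|---|---|---|
| 0.3 | 55% | 73% |
| 0.5 | 66% | 79% |
| 0.7 | 87% | 92% |
| 0.8 | 97% | 98% |

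Repeat runs differ by one or two points. At r = 0.5, the change score with no screening had 68%. The 13-point gap (79 − 66) therefore splits into 68 − 66 = 2 points for screening and 79 − 68 = 11 points for change score versus ANCOVA.

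**6. A separate prognostic covariate** (correlation 0.5 with outcome, effect 0.8 SD):

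| Per arm | No adjustment | Adjust only if flagged | Prespecified |
|---|---|---|---|
| 15 | 0.56 | 0.56 | 0.67 |
| 20 | 0.69 | 0.70 | 0.80 |
| 30 | 0.85 | 0.86 | 0.93 |

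Screening performs almost exactly like no adjustment. Its type I error at this correlation was about 0.042, against about 0.05 for the prespecified model.

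**The case against.** The strongest reply is that the T1 outcome is not lost at all: it is the pre level of Time in every efficacy model. That is right. A reader might infer that the baseline score enters the analysis only in the 5% or so of trials where it happens to differ. The article does not support this; what happens about 5% of the time is that T1 is added again, as a covariate. What remains is that a change-score comparison does not adjust for baseline in the way ANCOVA does.

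A reader might also put the whole power gap down to the screening step. Step 5 shows otherwise: about 2 of the 13 points at r = 0.5 are due to screening. The gap also depends on r and nearly closes at 0.8.

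The wording is softer than a mechanical rule. It speaks of potential covariates, so a flagged variable need not enter and others are not expressly barred. That stands, but no other criterion is given, and unstated discretion after seeing the data is no safeguard. A separate analysis plan may list covariates, so their absence from the article is not the point. The point is the selection rule that the article does state.

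Finally, this is a feasibility trial of preliminary efficacy, and the rule does not raise the false-positive rate; if anything the test becomes slightly conservative. This bears on severity and is accepted.

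**Conclusion.** The point holds as a should-fix. The stated tests cannot identify useful covariates in a concealed, stratified randomised trial: they flag about 5% of variables at random at an assumed alpha of 0.05, and the stratifier almost never. The usual result is a model without prognostic covariates or the ACE-III stratum; the occasional result is one shaped by a chance imbalance.

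Screening by itself costs about 2 points of power and brings no gain. The larger loss against ANCOVA on T1, from about 18 points at r = 0.3 to about 1 point at r = 0.8, comes mainly from the change-score form of the 2 × 2 test. These power figures rest on an assumed sample size, effect and correlation. The flagging rate rests only on the assumed alpha.

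The documents do not support a claim of inflated type I error or of an invalid primary conclusion. The harm is lost precision and a model that depends on the data.

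**What to change.** In Data Analysis, delete the t-test screening step. State that the pre-post models comparing CO-OP-I with WLC adjust for the T1 value of the outcome and the ACE-III stratum, whatever imbalance is observed. Any further covariate should be named in advance on prognostic grounds. Present baseline characteristics descriptively by group, without p-values.

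For GAS, adjusting for T1 may add little, because Primary Outcome Measures sets the baseline level at −1; the ACE-III stratum still applies there.

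The cost is a short edit to the analysis section and about two degrees of freedom per model. No new data are needed, since the T1 outcomes and ACE-III are already collected.

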## Method

### Design and Setting

A parallel-group assessor-masked randomized controlled feasibility trial using blocked allocation (6 per block) to enable equal ratios between treatment and control groups. Intensive CO-OP (CO-OP-I) training will be compared to WLC to establish preliminary efficacy. Following a non-intervention period, the WLC will then undertake standard CO-OP (CO-OP-S) (Figure 1). A mixed-method approach will be used to assess feasibility in terms of acceptability, demand, implementation, practicality, adaptation, integration, expansion, and limited-efficacy testing (Bowen et al., 2009). The study was approved by the UQ Human Research Ethics Committee (HREC) — 2020/HE002650 on February 9, 2021.

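### The pre-post 2 × 2 ANOVA is valid but less precise than a model with baseline score and ACE-III stratum, and the baseline t-test rule would seldom supply either

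*Protocol article*

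**What the plan says.** The Data Analysis section of the protocol article fixes the model: "A series of 2 × 2 (Treatment×Time) mixed between-within ANOVAs will be conducted with intention to treat analysis". Its first use is to "compare the CO-OP-I group with WLC to determine preliminary efficacy (Time: pre, post"; the second applies the same two times to self-efficacy and health-related quality of life. These are comparisons (1) and (2). Comparison (3), on intensity and follow-up, is not at issue here.

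The same section does provide for covariates. Independent-sample t-tests will look for "differences in baseline characteristics between groups to identify potential co-variates for inclusion in the main analysis".

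Randomisation is stratified. Random Allocation describes assignment "using blocked allocation, stratified by scores on the ACE-III". Demographic and Disease Data adds "The stratification groups are no cognitive impairment and MCI" (scores 89–100 and 77–88), and Design and Setting specifies blocks of 6. Data Analysis does not name ACE-III as a model term.

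On missing data, Data Analysis says "Missing data will be examined to determine if missing completely at random". The same sentence then provides for multiple imputation where it proves necessary.

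**The concern.** Three choices fixed in the text work against precision.

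- The interaction in a two-time mixed ANOVA subtracts the whole baseline score instead of weighting it by how well it predicts the post score.
- Covariates are chosen by whether the arms happen to differ at baseline, not by whether the variable predicts outcome. In a randomised trial such differences are chance. A factor balanced by stratification is the one least likely to be flagged.
- Imputation can be read as conditional on an MCAR check.

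At stake are wider intervals than the collected data allow, and a model not known until the baseline data are seen. The trial is meant to give preliminary efficacy estimates that prepare larger trials, so the width of those intervals matters.

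**Working it through.** **Inputs from the protocol article.** Two arms, 1:1 allocation in blocks of 6; two ACE-III strata; two times for comparisons (1) and (2); GAS baseline scaled at −1.

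**Inputs assumed.** The article gives no sample size, alpha, power, SD or pre-post correlation r, so there is no planned figure to reproduce. I take r from 0.3 to 0.9, equal SDs at T1 and T2 (set to 1), an effect of 0.8 SD, two-sided alpha 0.05, 80% power, and total N between 24 and 48.

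**Step 1: equivalence.** On one simulated data set with 18 per arm and no covariate, the interaction F was 5.8846 and the squared change-score t was 5.8846.

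**Step 2: large-sample precision.** Var(change) ∝ 2(1−r) and Var(ANCOVA) ∝ 1−r². The ratio is (1−r²)/[2(1−r)] = (1+r)/2. Sample size and power use the normal approximation.

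| r | 2(1−r) | 1−r² | Ratio | n per arm, change → ANCOVA | Power at 18 per arm, change → ANCOVA |
|---|---|---|---|---|---|
| 0.3 | 1.40 | 0.91 | 0.65 | 35 → 23 | 53% → 71% |
| 0.5 | 1.00 | 0.75 | 0.75 | 25 → 19 | 67% → 79% |
| 0.7 | 0.60 | 0.51 | 0.85 | 15 → 13 | 87% → 92% |
| 0.9 | 0.20 | 0.19 | 0.95 | 5 → 5 | 100% → 100% |

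As extra participants needed by the change-score test: 1/0.65 = 1.54, 1/0.75 = 1.33, 1/0.85 = 1.18 and 1/0.95 = 1.05, that is 54%, 33%, 18% and 5% more.

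**Step 3: small samples.** I compared the change-score test with ANCOVA on T1 plus stratum, 3,000 simulated trials per setting. The simulated stratum had no effect on outcome, so this shows the gain from T1 after paying for an idle stratum term.

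- Total N = 24: power 48% v 57% at r = 0.5; 68% v 72% at r = 0.7.
- Total N = 36: power 65% v 76% at r = 0.5; 86% v 89% at r = 0.7.
- Type I error: 4.7–5.2% for the change score, 4.8–5.7% for ANCOVA.

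A separate simulation of the variance ratio gave 0.77–0.79 at r = 0.5 and 0.92–0.95 at r = 0.8. At r = 0.9 it was 1.00 with 10 per arm and 0.97 with 20. At r = 0.95 it was 1.03 and 1.01.

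**Step 4: covariate rule.** With a 0.05 threshold (assumed), an unstratified baseline variable is flagged in about 5% of trials, whatever its prognostic value. For ACE-III I simulated stratified blocks of 6, about half the sample in each stratum, 4,000 trials each at N = 24, 36 and 48. The baseline t-test flagged the ACE-III score in 0.1%, 0.0% and 0.0% of trials, and the stratum indicator in 0.0% at every N.

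**Step 5: GAS.** If every baseline is −1, change = T2 + 1. The change-score test is then the same as a comparison of T2 scores, and T1 carries no information.

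**Step 6: missing data.** One sentence first checks for MCAR, then makes imputation conditional. One reading is that imputation follows whenever data are missing. The other is that it follows only if MCAR is rejected. Under the second, an MCAR test with little power in a small trial would often not reject. The ANOVA needs complete pairs, so incomplete cases would drop out. Non-rejection does not establish MCAR.

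**The case against.** The strongest reply is that the planned test is sound. Type I error is close to 5%, and the trial is about feasibility and preliminary efficacy, so a more efficient model is a preference. The first part stands: nothing here shows invalidity. The second does not remove the point, because the gain uses only data already collected.

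Several stronger readings are tempting and are not supported:

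- *The analysis is unadjusted.* It is not; the section provides for covariates. The weakness is how they are chosen.
- *Incomplete cases are simply left to an MCAR test.* Multiple imputation is planned. Only its trigger is unclear, and details of the imputation model may sit in an analysis plan that is not shown.
- *Complete-case change scores are unbiased only under MCAR.* This is too strong. With 20 per arm and a true effect of 0.8, simulated dropout that depended on arm alone (35% v 10%) left the estimate at 0.80. Dropout depending on arm and a stable personal trait did the same, since differencing removes the trait. Other mechanisms can bias it.
- *A change score is never more precise than ANCOVA.* This holds in large samples. Step 3 shows parity or a slight reversal at r of 0.9 or above with small arms.
- *Every efficacy outcome loses precision.* GAS, a primary outcome, does not gain from baseline adjustment.

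It is also fair that a change score already removes stable differences in level between strata. The stratum term helps only if cognition predicts outcome beyond that, which the article does not establish.

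**Conclusion.** The point holds as one of precision, not validity. For COPM, PDQ, NEADL and the self-efficacy and quality-of-life scores, comparisons (1) and (2) give up about 35%, 25%, 15% or 5% of the large-sample variance at r = 0.3, 0.5, 0.7 or 0.9. In the small-sample simulations the power difference was 9 to 11 points at r = 0.5 and 3 to 4 points at r = 0.7. All of this rests on an assumed r, equal SDs, a 0.8 SD effect and assumed arm sizes. The value of the stratum term is not quantified.

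The covariate rule does not make good the loss. It admits variables on chance imbalance and, under the stated simulation assumptions, flags ACE-III in about 0.1% of trials or fewer. The missing-data point is secondary and concerns ambiguous wording: a reader might infer a planned complete-case analysis, but the text does not say so.

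**What to change.** - For comparisons (1) and (2), estimate the CO-OP-I minus waitlist difference at T2 from a model with arm, the T1 score of that outcome and ACE-III stratum, with a 95% CI. For GAS the T1 term has little or nothing to contribute.
- Fix the covariates in advance and drop the baseline t-tests as the rule for choosing them.
- State that whenever T2 is missing, multiple imputation or a baseline-adjusted mixed model on all available scores will be used, whatever an MCAR test shows.

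The cost is analysis wording only. T1 scores and ACE-III are already collected before allocation.
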